#### Secondary outcomes

In population health intervention research, the effects of an intervention are modified by the characteristics and dynamics of the context in which it is deployed, so including interactions between the intervention and its context will be a methodological challenge [23]. Even if not controlled, factors such as the actions of the stakeholders in prevention will be prospectively registered in a dedicated database and will be included in the model.

Other factors will remain unknown and will contribute to a residual contextual variance which may remain significant even after adjustment for individual variables. Furthermore, to explore contextual effects and to throw light on the causal mechanisms contributing to the effectiveness of the intervention, quantitative analyses will be complemented by a qualitative approach based on approaches that have emerged in realistic randomized controlled trials, using a theory that goes beyond logical models to describe contextual mechanisms and contingencies [24]. An intervention theory is currently being developed and an auto-questionnaire will specifically explore the components of the Com B model (Capacity, Opportunity, Motivation) used by women thanks to the interventions (MMU, preventive action, MMU-specific information tools) [25–27]. A second auto-questionnaire will specifically evaluate their informed choices with the MMU-specific information tools, and a third will probe their level of satisfaction. In order not to call upon the same women several times, we will randomly select three groups of women from the intervention and control arms. Apart from the questionnaire on satisfaction which will be sent only to participating women a few weeks after their participation, the other two questionnaires will be sent to both participants and non-participants.

A medico-economic evaluation will also be performed. A cost-effectiveness analysis of invitation to the MMU (or to a radiologist office) versus invitation to radiologist office (RO) only (usual screening) will thus be conducted from the payer perspective over a period of 2 years, i.e. the duration of a screening campaign. It will determine the efficiency of the invitation to the MMU compared to RO only. The economic evaluation will provide an ICER (incremental cost-effectiveness ratio), which will represent the incremental cost per additional screening of the invitation to MMU compared with the usual screening procedure. A similar approach was already applied for the retrospective analysis of the Orne department MMU [28].

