**Methods:**

A collaborative project will be conducted as a randomized controlled cluster trial in 2022–2024 in remote areas of four French departments. Small geographic areas were constructed by clustering women eligible to OBCS, according to distance to the nearest radiology centre, until an expected sample of eligible women was attained, as determined by logistic and financial constraints. Intervention areas were then selected by randomization in parallel groups. The main intervention is to propose an appointment at the mobile unit in addition to current OBCS in these remote areas according to the principle of proportionate universalism. A few weeks before the intervention, OBCS will be promoted with a specific information campaign and corresponding tools, applying the principle of multilevel, intersectoral and community empowerment to tackle inequalities.

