#### Intervention description: preventive actions

About 2 weeks before the MMU is parked at the appointment site, the women concerned receive information about it. For most women, this is the first time they learn of the existence of the MMU.

The stakeholders provide various forms of information on OBSC and on the organization of screening in the MMU. A dedicated decision-making tool has been developed for this purpose. All those involved have been informed about the need to adhere to the protocol and the importance of respecting the intervention and control groups. Preventive actions are organized in collaboration with the research team and are targeted mainly on the women in the intervention group. However, in the areas where the intervention takes place, preventive actions undertaken prior to the MMU visit are organized by and under the responsibility of the stakeholders according to the territory they cover and their availability. In addition, a dedicated website https://mammobile-normandie.fr/ provides further downloadable information including a video of screening in the MMU and the times and days when it will be parked in their vicinity.

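### Stakeholder prevention actions, a post-randomisation part of the intervention, are to enter an unspecified model; the arm coefficient of any model containing them is not the intention-to-treat effect

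*Protocol article*

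**What the plan says.** Under Secondary outcomes the protocol article introduces the interplay of intervention and context, and then states that "the actions of the stakeholders in prevention will be prospectively registered in a dedicated database and will be included in the model". The same section counts preventive action among "the interventions (MMU, preventive action, MMU-specific information tools".

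The section Intervention description: preventive actions says these actions are "targeted mainly on the women in the intervention group", and that in intervention areas they are "organized by and under the responsibility of the stakeholders according to the territory they cover and their availability". The abstract describes the campaign alongside the intervention: "A few weeks before the intervention, OBCS will be promoted with a specific information campaign and corresponding tools".

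Under Primary outcomes, participation is compared by arm in intention to treat in two ways. One is a raw and age-standardised comparison of clusters. The other is a multilevel logistic regression adjusted for deprivation, age and other available individual characteristics. Stakeholder actions are not named among those covariates.

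**The concern.** The Secondary outcomes sentence speaks of the model as though it were already defined, and the multilevel logistic regression is the only one defined. The sentence that follows, on contextual variance left over after individual adjustment, fits that regression too. A reader could therefore take the actions to be extra covariates in the individual-level effectiveness model.

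Allocation causes much of the exposure to these actions. Adjusting for them compares arms at the same level of preventive action, which is not the contrast that was randomised. The result is meant to inform national rollout, so it matters whether a reported arm effect belongs to the whole package or to the mobile unit offer with the campaign held fixed.

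**Working it through.** **Step 1: status of the actions.** Three features are in the text.
- Part of the intervention: they have their own heading under Intervention description, and the Secondary outcomes section lists them with the interventions.
- After allocation: Allocation reports randomisation as done, and the actions precede each visit of the mobile unit, the first being in March 2022.
- Unequal by arm and not randomised: they are aimed mainly at the intervention arm and depend on stakeholders' territory and availability. The Discussion (Reducing inequalities) adds that the screening structure acts where participation is low.

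**Step 2: what the arm coefficient becomes.** Let logit(participation) = a + d·arm + g·action + cluster effect, with action present in a share πI of intervention clusters and πC of control clusters. Without the action term, the arm coefficient is approximately d + g(πI − πC). With it, the coefficient is d. The share removed is g(πI − πC) / [d + g(πI − πC)]. If an arm-by-action term is added, the arm main effect is the effect at zero action.

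The article gives no value for d, g, πI or πC, so all are assumptions. A simulation used 178 + 178 clusters, 258 women each (91,982/356 = 258.4), the stated intraclass correlation of 0.0083 and 48% participation (the national figure from the Background). It ran 400 times per row, with linear regression on cluster empirical logits. As a check on the inputs, the article's design effect reproduces: 1 + (318.6 − 1) × 0.0083 = 3.636, against 3.63 stated.

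| πI v πC | d, g | Formula: without → with action term | Simulated | Removed (formula) |
|---|---|---|---|---|
| 60% v 10% | 0.06, 0.06 | 0.090 → 0.060 | 0.088 → 0.059 | 33% |
| 80% v 10% | 0.06, 0.06 | 0.102 → 0.060 | 0.102 → 0.060 | 41% |
| 90% v 10% | 0.03, 0.09 | 0.102 → 0.030 | 0.100 → 0.028 | 71% |
| 80% v 10% | 0.06, 0 | 0.060 → 0.060 | 0.059 → 0.059 | 0% |
| 50% v 50% | 0.06, 0.06 | 0.060 → 0.060 | 0.060 → 0.060 | 0% |

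Nothing is removed if the actions do not work or are equally common in both arms. The article says they are not equally aimed at both arms.

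**Step 3: precision.** With 1:1 allocation and one binary action indicator per cluster, p = (πI + πC)/2, r = 0.25(πI − πC)/√[0.25·p(1 − p)], and the standard error of the arm coefficient is multiplied by √[1/(1 − r²)].

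| πI v πC | r | 1/(1 − r²) | Standard error |
|---|---|---|---|
| 60% v 10% | 0.52 | 1.38 | × 1.17 |
| 80% v 5% | 0.76 | 2.36 | × 1.53 |
| 90% v 5% | 0.85 | 3.63 | × 1.90 |

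The 3.63 in the last row is a variance inflation factor; its match with the design effect is coincidence. This loss remains when the actions have no effect: in the 80% v 10% row of Step 2 with g = 0, the standard error goes from 0.022 to 0.031.

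**Step 4: confounding.** Take 80% v 10% and d = g = 0.06. Assume a correlation of 0.5 between a cluster's underlying participation and its propensity to receive an action. The cluster standard deviation is √[(0.0083/0.9917) × π²/3] = 0.166. The action coefficient is then biased by 0.5 × 0.166 × (0.280 + 0.175)/0.25 = 0.151. Here 0.280 and 0.175 are the normal densities at the 80% and 10% points, and 0.25 = 0.8 × 0.2 + 0.1 × 0.9. The arm coefficient shifts by 0.7 × 0.151 = 0.106 in the opposite direction.
- Actions placed where participation is already higher: 0.060 − 0.106 = −0.046 (simulated −0.045).
- Actions placed where participation is lower: 0.060 + 0.106 = 0.166 (simulated 0.166).

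In both cases the model without the action term still returns about 0.102. Adjustment can therefore move the estimate either way.

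**The case against.** The case on the other side is substantial. The sentence stands under Secondary outcomes and serves objective (c), understanding context and mechanisms; it opens by treating the actions as uncontrolled context. Primary outcomes names its covariates without the actions, and the raw and age-standardised comparison contains no post-randomisation variable on any reading. The Mixed evaluation section already foresees using the action data to learn how information can be improved. The main intervention is defined more narrowly as the offer of an appointment at the mobile unit. How context terms enter a secondary model is commonly left to a fuller document.

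Most of this stands, and it limits the reach of the point. A reader might infer that the trial's primary effect estimate is compromised, or that a real gain would be lost. The article does not support that: the cluster-level intention-to-treat comparison is planned regardless. A reader might also infer that adjustment must understate the effect, or carry the standard-error inflation over to the trial's stated detectable difference of 1.5%. Step 4 shows that the direction depends on where stakeholders act, and the detectable difference is stated for the primary comparison, not for a context model.

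What does not stand is that nothing needs changing. The narrower definition of the main intervention does not help, because actions triggered by allocation are post-randomisation variables under either definition. Nor is this an omitted detail: the article positively states an inclusion and does not say in which model.

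**Conclusion.** The point holds as a should-fix. Any model containing the stakeholder actions gives an arm coefficient that is not the intention-to-treat effect of the package, and the article leaves open whether its individual-level effectiveness model is such a model. The cluster-level comparison is unaffected, as is the individual-level regression if fitted only with its named covariates.

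The size cannot be derived from the document. Under assumed action frequencies the standard error rises by about 17% to 90%. Under assumed working actions with unequal exposure, roughly a third to seven tenths of the log odds ratio leaves the arm coefficient. Non-random placement could shift it further in either direction. These figures illustrate the mechanism and do not forecast this trial's results. They assume one binary action indicator per cluster and a main-effect adjustment.

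**What to change.** Under Primary outcomes, state that the individual-level effectiveness model contains only arm and pre-randomisation covariates (deprivation, age and other baseline characteristics), and that its arm coefficient estimates the effect of the whole package: the mobile unit offer, its invitation and the preventive actions.

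Under Secondary outcomes, replace the reference to the model with a separately labelled, non-randomised analysis for objective (c). This could describe how participation varies with the type and number of actions within intervention clusters, or be a formal mediation analysis with its assumptions stated.

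The cost is a few sentences, settled before analysis. The action register is still collected and used in full, and the design and sample are unchanged.

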### Governance and monitoring

#### Steering committee

A steering committee was formed at the start of the project with one or two representatives from the main partners. Scientific decisions are made in partnership with the SMS. The frequency of meetings has gradually increased to one per week. The SMS database complies with the regulations in force on the protection of health data. Procedures for the circulation, recording and extraction of data relating to project monitoring have been drafted in order to guarantee the quality and confidentiality of the data.

#### Data monitoring committee

We did not set up a data monitoring committee because what we are evaluating is a new modality for offering breast cancer screening, the MMU, and not the screening act. Protocol modifications will be discussed with partners and funders and if necessary, submitted for ethics committee approval. The trial registration will be updated.

#### Dissemination plans

Results will be published in research publications and conference contributions. Feedback will also be provided to all partners. Scientific reports will be written for funders. The datasets analysed during the current study and statistical code are available from the corresponding author on reasonable request, as is the full protocol.

## Discussion

This population health intervention research involves a wide range of stakeholders who must coordinate their actions according to the conditions and the environment in which they are implemented. The protocol must provide evidence of the effectiveness of the MMU and show that it reduces inequalities in participation in OBCS. At each stage, i.e. protocol, implementation and evaluation, the project must incorporate the existence and the reduction of these inequalities [29].

### Reducing inequalities

The co-construction of this project by teams of researchers, institutional and local stakeholders from different disciplines inside and outside the health field is a real strength since it ensures that the study is comprehensive and multidisciplinary. This will facilitate its implementation and subsequent uptake by all those involved in it. A wide range of professionals from the medical, medico-social, social and associative field will play an active role. Although prevention is the main focus of the intervention, the social and psychosocial dimensions of the subjects will also be considered. Our hope is that women will become more receptive to the need for prevention thanks to this campaign.

Nevertheless, it is a challenge to bring all of the stakeholders onboard and focused on a common goal. The project is time-consuming and was already agreed upon 3 years ago. Some aspects of the project are the responsibility of the partners, so the research team leading it does not have full control over the entire project. For example, the MMU is purchased by the four departments involved in the project, so all the administrative stages of the purchase have to be validated by several levels of authority. However, the SMS is the central partner because of its key role in organizing OBCS, even in remote areas, and women largely understand this. The SMS also undertakes preventive actions in areas where the participation rate is low, and it has established a network of partners to offset this weakness. This network will continue to assist in the operation of the MMU at the end of the two years of the intervention. Thereafter, the MMU will continue to function outside of the constraints of the protocol. Another challenge will then be to incorporate other disciplines such as geography and social psychology into the project. This will be difficult but necessary: on the one hand, different disciplines use different research tools and semantic registers; on the other, fully evidence-based conclusions can be drawn only by including the input of research domains that throw fresh light onto issues that the medical community is unable to investigate alone.

The project is based on consensual models of the social determinants of health, which take individual behaviours and characteristics (proximal determinants) into account and the living environment (distal determinants or causes of causes) in a causal model of inequalities in health [30]. In the typology of interventions to reduce the social inequalities stemming from the dynamic model of the WHO, this is a multilevel intervention operating at access to service, community and individual level. By factoring the MMU into the current breast screening campaign, our design will meet the requirements of the principle of proportionate universalism by providing an additional screening modality for women living far from a radiologist’s office, thus empowering them and reducing the inequalities from which they suffer. In turn, the community in the wider sense will become empowered. Finally producing information adapted to the target population and based on the literacy principle will improve women’s knowledge about OBCS.

### Design

This randomized cluster trial will provide the highest level of evidence to date regarding the effectiveness of an MMU in enhancing the OBCS participation rate in remote areas. The approach is territorial based on administrative units, the intervention targets women who live far from radiology centres approved for screening, and the clusters are randomized into parallel groups. Other designs such as stepped-wedge and cross-over have been studied, but they are not applicable with an MMU that has to move optimally from one area to another [31]. Nevertheless, parallel group randomization carries a risk of bias. Since the main criterion is the distance to the radiology centre, the zones that are randomized are neighbouring. Consequently, even if only women residing in a given intervention area receive an appointment to attend the MMU, information may cross boundaries between areas. Therefore, this potential bias will be monitored.

Another limitation is that the MMU is dedicated to populations living far from radiology offices. Therefore, even if the value of the intervention is proven to be positive, it will demonstrate the potential for the MMU to reduce territorial inequalities but not necessarily social inequalities. For some deprived women, the obstacle to screening participation may be more social or cultural than simply their physical access to a radiologist. In addition, while remote populations are globally less deprived than urban populations, some individuals living in rural areas may be heavily deprived. For this reason, future work will investigate the impact of deploying the MMU in urban areas.

### Mixed evaluation

While this protocol will assess the potential of using the MMU to reduce territorial inequalities, it also contains contextual factors for identifying the conditions in which it could be rolled out nationwide with maximal efficiency. First, we will gather heterogeneous data on what actions or information campaigns have been carried out before the MMU arrives in a given vicinity, and on who provided the information. In turn, this will demonstrate how that information, and how it is given, can be improved. Although a set of well-intentioned stakeholders interact with each other at present, much of that interaction takes place on a piecemeal basis with insufficient overarching global vision. The planned MMU intervention will partly resolve this issue by mobilizing a network of stakeholders to harmonize sources of knowledge, modify the roles they play, and by adapting them to a set of newly emerging constraints, some of which may be as yet unknown. However, they may include issues pertaining to demography, geography, and even political decisions. Ultimately, the information that this study will generate is likely to be useful not only at national level but also in other European countries.

## Conclusions

Providing conclusive data and new knowledge about the mechanisms of participation in OBCS remains a major public health issue. This article presents the design of a clustered randomized trial to evaluate an MMU used for OBCS to reduce territorial inequalities in a remote area of France. Its overarching objective is to reduce health inequalities. Several contextual factors will need to be taken into consideration in this complex population health intervention, so the analysis of the data must be fine-grained. Much care will be taken from the design stage to the publication of our findings to make sure that the mechanisms underpinning the results and the modalities for transfer to other French or European regions are based on robust evidence.

### Trial status

The published protocol corresponds to the protocol at the start of the intervention. The clusters were defined in October 2019. The first invitations were sent on February 18, 2022, and the first intervention will take place on March 2, 2022. The intervention must take place in 4 departments, for 2 years. With all the hazards of interventional research, we expect an end of intervention for March 2024.

## Data Availability

The datasets analysed during the current study are not publicly available before the end of the analyses of the intervention. Any data required to support the protocol can be supplied on request.

## Abbreviations

AAPRISS: Apprendre et Agir Pour Réduire les Inégalités Sociales de Santé
BC: Breast cancer
CNIL: Commission Nationale de l'Informatique et des Libertés
EDI: European Deprivation Index
ICER: Incremental Cost-Effectiveness Ratio
IDEES: Identité et Différenciation de l*’*Espace, de l*’*Environnement et des Sociétés
INSERM: Institut National de la Santé et de la Recherche Médicale
IRIS: Ilots Regroupés pour l’Information Statistique
IRTS: Institut Regional du Travail Social
MMU: Mobile Mammography Unit
OBCS: Organized Breast Cancer Screening
PSN: Promotion Santé Normandie
RCT: Randomized Cluster Trial
RO: Radiologist Office
SMS: Screening Managing Structure
WHO: World Health Organization
